**Methods and results::**

The risks and the benefits of both options (PCI and OMT) were listed in a CTO decision aid (DA). Eligible participants detected by invasive coronary angiography (ICA) or coronary computed tomography angiography (CCTA) were divided into PCI or OMT groups according to patients’ choice after shared-decision making process with DA. Participants will undergo positron emission tomography/computed tomography (PET/CT), cardiac magnetic resonance (CMR) and transthoracic echocardiography (TTE), and proceed to ICA and revascularization if possible. Blinded core laboratory interpretation will be performed for ICA, CCTA, PET/CT, CMR, and TTE. All participants will be followed up for 12 months. The primary endpoint is the improvement to the decrease of myocardial viability from baseline assessed with the use of PET/CT after 12-month follow-up.

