### Myocardial F-18 FDG PET/CT

4.3

Myocardial F-18 FDG PET/CT was performed within 2 days of each other. After an overnight fasting for at least 12 hours, an oral glucose of 10 to 50 g was given to the patients according to their serum glucose level. For diabetics, acipimox was administrated (500 mg; oral dose) before glucose loading. Insulin was intravenously administrated if the blood glucose level >9 mmol/L at 45 minutes after oral glucose administration with close monitoring of blood glucose. When the blood glucose level was appropriate, F-18 FDG (3 MBq/kg) was administered intravenously. Images were acquired 1 to 2 hours after tracer injection using a Biograph mCT 128 PET/CT scanner (Siemens Medical Solutions, Knoxville, TN) equipped with high-performance LSO PET crystals and a 128-slice CT. After a scout CT acquisition (120 kV, 10 mA) used for proper patients positioning, a CT transmission scanning (140 kV, 35 mA) was performed for attenuation correction and anatomical localization. Images were reconstructed using TrueX+TOFUltralHD reconstruction (21 subsets, 4 iterations). The Cedars software (Cedars-Sinai Medical Center, Los Angeles, CA) for phase analysis was applied on F-18 FDG PET/CT scans.

Nongated SPECT images were used for myocardial perfusion assessment by Quantitative Perfusion SPECT. Perfusion defect extent was expressed as a percentage of the whole myocardium area. Scar burden and myocardial viability were assessed by 2 experienced nuclear physicians. Segments with tracer uptake < 50% were considered transmural infarcted myocardium. F-18 FDG PET images were read in combination with rest SPECT images for myocardial viability assessment. The patterns of perfusion-metabolism mismatch and normal perfusion irrespective of F-18 FDG uptake signified viable myocardium whereas perfusion-metabolism match signified myocardial scar or nonviable tissue. The extent of viable myocardium and scar was expressed as percent of the LV area (%).

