### Primary endpoint

5.1

The primary study endpoint of the SOS-comedy trial is changed to myocardial viability from baseline assessed with the use of PET/CT system during 12-month follow-up.

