## Statistical analysis

8

Normally distributed continuous variables were presented as the mean ± SD, variables with a skewed distribution as the median together with interquartile range (IQR). Categorical variables are expressed as percentages. Changes in data measured by PET/CT, CMR, and TTE will be summarized by mean, standard deviation, minimum, median, and maximum. Differences between groups, including baseline characteristics, will be compared using a *t* test, Wilcoxon rank-sum test, or *χ*^2^ test. The correlation between treatment strategies and viable myocardium will be analyzed by liner regression analysis.

For the safety evaluation, the number and prevalence of MACEs will be calculated. The Kaplan–Meier method was used to illustrate the timing of events during follow-up in relation to treatment strategies and statistical assessment was performed with the log-rank test. The prognostic value of treatment strategies was assessed by investigating its relation with the composite outcome in Cox proportional-hazards analyses.

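### As worded, the viability regression takes the amount of viable myocardium as its outcome and names no baseline term, while the primary endpoint is change from baseline.

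*Protocol article*

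**What the plan says.** All references are to the protocol article.

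- **Endpoint.** The Primary endpoint section gives it as "changed to myocardial viability from baseline assessed with the use of PET/CT system during 12-month follow-up". The Abstract calls it "the improvement to the decrease of myocardial viability from baseline assessed with the use of PET/CT after 12-month follow-up". The wording is rough, but both passages describe a within-patient difference between two scans. The Sample size calculation section also names improvement in viability as the main goal.
- **Measured variable.** Under Myocardial F-18 FDG PET/CT: "The extent of viable myocardium and scar was expressed as percent of the LV area". This is a quantity read from one scan.
- **Analysis.** The Statistical analysis section has three relevant sentences. On description: "Changes in data measured by PET/CT, CMR, and TTE will be summarized by mean, standard deviation, minimum, median, and maximum". On comparison: "Differences between groups, including baseline characteristics, will be compared using a *t* test, Wilcoxon rank-sum test, or *χ*^2^ test". On modelling: "The correlation between treatment strategies and viable myocardium will be analyzed by liner regression analysis". The modelling sentence gives no time point, does not mention change and names no covariate. None of the three is called the primary analysis.
- **Allocation.** Participants "were divided into PCI or OMT groups according to patients’ choice after shared-decision making process with DA". There is no randomisation.
- **Data.** The Participants section schedules PET/CT at baseline and at 12 months, so each patient is meant to have both scans.

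**The concern.** The regression is the only model named for viability, and its stated outcome is not the stated endpoint. Two sentences earlier the section refers explicitly to changes in the PET/CT data. The regression sentence does not.

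In a randomised trial the cost would be mainly precision. Here patients choose their treatment, so mean baseline viability need not be equal. The Introduction itself argues that patients without viability or with little ischaemia could not be expected to gain from the procedure, which makes baseline viability a plausible influence on the choice. A model of the 12-month amount without a baseline term would report a pre-existing difference as if treatment had produced it. The test of changes and the regression could then point different ways, and the article does not say which one decides.

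**Working it through.** The plan gives no figure for this point, so there is none to reproduce. The documents give no SD, between-visit correlation, baseline gap or allocation ratio. Every such value below is an assumption.

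**1. What each model estimates.** Let g be the baseline gap (PCI minus OMT) and rho the correlation between the two scans, with equal SDs at both visits. Suppose there is no true difference in change, so the gap persists to 12 months. The expected treatment coefficients are:

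- 12-month amount on strategy alone: g
- change on strategy alone: 0
- 12-month amount on strategy and baseline: (1 - rho) x g
- change on strategy and baseline: (1 - rho) x g

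The last two are identical because subtracting baseline from the outcome lowers only the baseline coefficient, by 1. It leaves the strategy coefficient unchanged.

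**2. Simulation check.** 2000 trials, 100 per group, assumed SD of 10 points of % LV area, true difference in change 0. Mean treatment estimate in points:

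| Gap | rho | Amount, unadjusted | Change, unadjusted | Amount or change, with baseline |
|---|---|---|---|---|
| 0 | 0.5 | -0.03 | -0.06 | -0.04 |
| 0 | 0.8 | -0.01 | 0.01 | 0.00 |
| 2 | 0.5 | 1.98 | 0.05 | 1.01 |
| 2 | 0.8 | 1.90 | -0.02 | 0.37 |
| 5 | 0.5 | 4.97 | 0.05 | 2.51 |
| 5 | 0.8 | 5.01 | 0.01 | 1.00 |

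The unadjusted model of the amount carries over the whole gap.

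**3. False-positive rate of the unadjusted model of the amount.** The planned 200 less the stated 15% drop-out is 200 x 0.85 = 170, or 85 per group if split equally. With g in SD units, the rate is P(|Z + g/sqrt(2/85)| > 1.96), and sqrt(2/85) = 0.1534.

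- g = 0.2: shift 0.2/0.1534 = 1.30, rate 0.256
- g = 0.3: shift 0.3/0.1534 = 1.96, rate 0.498

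The Interventions section reports 240 enrolled. The same steps give 240 x 0.85 = 204, or 102 per group, and rates of 0.298 and 0.572.

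**4. The same null for the baseline-adjusted model.** Bias is (1 - rho) x g and the SE is about sqrt((1 - rho^2) x 2/85). At g = 0.3:

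- rho = 0.7: 0.09/0.1095 = 0.82, rate about 0.13
- rho = 0.5: 0.15/0.1328 = 1.13, rate about 0.20

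Adjustment shrinks the carry-over but does not remove it under this null.

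**5. Variance of the treatment estimate, relative to the unadjusted amount (1.00).** Change: 2(1 - rho). Baseline-adjusted: 1 - rho^2.

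| rho | Change | Baseline-adjusted |
|---|---|---|
| 0.3 | 1.40 | 0.91 |
| 0.4 | 1.20 | 0.84 |
| 0.5 | 1.00 | 0.75 |
| 0.7 | 0.60 | 0.51 |
| 0.8 | 0.40 | 0.36 |

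The change score is more precise than the 12-month amount only if rho exceeds 0.5.

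**The case against.** The strongest reply is that one loose sentence is being read as a model specification. It fixes neither a time point nor a covariate list. The surrounding text is about change, and the article's phrasing is imprecise elsewhere, including in the endpoint definition. Viable myocardium may simply be shorthand for its change. Covariates are commonly left to a fuller plan, which is not shown here. The t or Wilcoxon comparison can already be applied to the changes, so the endpoint has a matching analysis.

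Much of this stands. A reader might infer any of three stronger claims, and the article supports none of them:

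- **That the trial will definitely model the 12-month amount without baseline.** This is the literal reading, but the text does not settle it.
- **That the outcome mismatch is a defect which covariates could not cure.** This is wrong. Once baseline viability is a covariate, amount and change give the same strategy coefficient.
- **That the primary endpoint has no suitable analysis.** The between-group tests can serve it.

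What the reply does not remove is that the outcome is stated, and as stated it differs from the endpoint. This is a mismatch within the article and not just detail left out. The two readings give different treatment estimates when the groups differ at baseline, so the sentence needs correcting on either reading.

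**Conclusion.** The point holds as a mismatch of wording with a real consequence if the sentence is followed literally. The regression names an amount, the endpoint is a change, and no baseline term is stated. In self-selected groups an unadjusted model of the 12-month amount would carry the full baseline difference into the treatment estimate.

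The size is conditional. The rates of about 26% and 50% require an assumed persistent gap of 0.2 or 0.3 SD, an assumed equal split of 85 per group, and the literal unadjusted model. They illustrate the mechanism and do not predict this trial's error rate. The variance figures depend equally on assumed correlations.

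It would also be too strong to infer that baseline adjustment settles the matter. If a baseline gap would persist without any treatment difference, the adjusted model keeps (1 - rho) times that gap and the change model keeps none. Which of the two suits the trial depends on how the groups would have evolved untreated, which the data cannot show. Neither handles other confounding by treatment choice. The correction is worth making because it is specific and almost free, but it does not overturn the design.

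**What to change.** Reword the regression sentence to state:

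1. The outcome is change in viable myocardium, 12 months minus baseline, in percent of LV. The model terms are treatment strategy and baseline viability. An equivalent statement is the 12-month amount with baseline as a covariate.
2. The result is the mean difference between strategies with its 95% CI.
3. The change model without the baseline term is reported alongside it.
4. Which of the two is primary is fixed before the outcome data are examined, with the reason, because they can differ in self-selected groups.
5. Neither estimate is claimed to remove other confounding by treatment choice.

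The cost is a few lines of text. Both scans are already scheduled for every patient, so no new data are needed. The one drawback is that two estimates will be reported, and any disagreement between them has to be explained.

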## Discussion and limitations

9

The last 5 years have been a significant increase in the number of publications focusing on coronary CTOs. The great majority of studies have compared successful with unsuccessful CTO PCI and only in recent years that the first trials specifically comparing CTO PCI with OMT have begun. The optimal treatment strategy for CTO patients is undetermined.

Several studies have shown that CTO-PCI is associated with clinical improvement.^[20]^ Cardona et al^[21]^ studied 29 patients with heart failure with reduced ejection fraction (HFrEF) and evidence of viability and/or ischemia within the territory supplied by the CTO, and improvement in ejection fraction, left ventricular end-systolic volume and ischemia burden was observed after CTO-PCI. Hwang et al^[22]^ compared clinical outcomes of PCI with those of OMT alone in patients with CTO of a single coronary artery. Four hundred thirty-five patients with CTO of a single coronary artery were analyzed. After a median follow-up duration of 47.6 months, MACEs were noted for 16 patients in the OMT group compared with 41 patients in the PCI group. After propensity-score matching, there were no significant differences between the OMT group and PCI group with respect to MACE frequency or cardiac death. However, the study did not routinely evaluate the amount of viable myocardium or ischemia of study patients using functional ischemia testing. One of the most critical steps in the management of the patients with obstructive coronary heart disease is to determine ischemic burden whether or not the patient is symptomatic. It is well known that stress radionuclide myocardial perfusion imaging (rMPI) may distinguish patients at high risk (more than 5% annual mortality rate) from those at intermediate risk (1% to 5% annual mortality rate) or low risk (<1% annual mortality rate).^[22]^ It was reported that the presence of extensive ischemia (extent of ischemia >10%), ischemia in multiple segments, ischemia in more than 1 coronary artery territory, LVEF < 45%, large fixed defects, transient or persistent left ventricular cavity dilatation and increased lung uptake of thallium on rMPI denotes high risk for increased risk of cardiac events.^[23–25]^ Safley et al^[26]^ showed that PCI in patients with CTOs significantly decreased the ischemic burden from 13.1% to 6.9%. In that clinical study most of the patients had moderate to severe ischemic burden before treatment. On the other hand, it was shown that there was improved survival following revascularization (PCI or CABG) only in the presence of moderate to severe baseline ischemic burden used by rMPI in coronary artery patients. The appropriate use criteria heavily emphasize ischemic burden and suggest that revascularization is appropriate in cases with large territories of ischemia, even without symptoms.^[27,28]^ Stuijfzand et al^[29]^ demonstrated that CTO patients with documented ischemia and viability showed significant improvement in stress MBF and a reduction of ischemic burden after successful percutaneous revascularization. However, the duration from PCI to follow-up imaging was 99 days, which may underestimate the effect of procedures. Second, the patients’ symptoms or quality of life before and after treatment were not sufficiently documented. Last, although the anatomical SYNTAX score is an important tool to establish the optimum revascularization approach in patients with complex coronary heart diseases including CTO, SYNTAX score II can better score than anatomical SYNTAX to reach the best treatment alternative. A combination of anatomical SYNTAX score with 3 simple clinical variables (age, creatinine, or creatinine clearance, LVEF) has been shown to contain most of the prognostic information in predicting mortality after PCI.^[30,31]^ From that point of view it should be better to use SYNTAX score II.

## Conclusions

10

This study will be the first multicenter study to evaluate the effect of PCI and/or OMT on myocardial viability in patients with single-vessel CTO using combined PET/CT during long-term follow-up. The patients were divided after shared decision making process, which can protect the interests of patients as well as increase compliance. Furthermore, the study will show the effects of PCI and/or OMT strategies on the clinical outcomes in patients with CTO of a single coronary artery. Thus, SOS comedy will indicate the optimal treatment modality for single lesions resulting in CTO.
